## Methods

### Study 1 Dynamic leg and arm training

#### Design

Study 1 is an explorative randomized controlled trial with multiple baseline measurements. Randomization is stratified according to the ambulatory status (ambulant/non-ambulant) of the boys and the boys are allocated to the intervention group or the control group in a 2:1 ratio. The intervention group receives dynamic exercise treatment, whereas the control group receives usual care (no specific intervention) during 24 weeks. After this period, the control group will also receive the physical training. Randomization is performed by an independent statistician. Despite randomization, differences in baseline characteristics between the intervention group and the control group may still be present due to the relatively small number of participants. For this reason, multiple baseline measurements are performed that will allow us to do within-subject analyses as well. Assessments are not blinded, because it was considered virtually impossible to prevent the boys from revealing their group allocation to the assessor.

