#### Intervention: dynamic leg and arm training

Boys train their legs and arms with bicycle training equipment (KPT Cycla, Kinetic, France). As this type of training equipment can be used actively or with electrical motor support, it allows a combination of active and passive bicycle training. Physical training is additional to any regular therapy or daily physical activity that boys already take part in, yet all possible co-interventions are registered.

Boys train at home or at school (depending on their preferences) during 30-min sessions (15 min leg and 15 min arm training), five days per week during 24 weeks. They are instructed to cycle with a continuous speed and stimulated to reach 700-1000 revolutions with both their legs and arms during each training session without getting too tired. Cycling characteristics are standardized (figure 3) and crank-arm length is adjusted to the child's height (e.g. a short crank-arm length for small legs and arms). Boys are free to choose when they would like to train, their training sequence (first arms or legs) and whether they want a break between the two 15 min training sessions or not. However, these training agreements are decided beforehand and registered in a training contract to which they should adhere. Additionally, the boys are recommended to train while watching television to make the training more pleasurable.

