**Figure 3 F3:**
[figure not shown]
Posture during dynamic leg and arm training

Based on general training principles and based on the results from previous training studies in boys with DMD and in animal models of DMD, the training intensity is low to moderate. Intensity is determined by an adjusted and modified Six-Minute Bicycle ergometer Test (see study outcomes). Boys are encouraged to reach as many revolutions as possible during this sub-maximal test. The number of revolutions is an indication for training intensity (level of electrical assistance). After six minutes of rest, boys cycle for three more minutes at the indicated training intensity. During this period, they should be able to cycle with a continuous speed of 60 revolutions per minute (RPM) with a perceived level of exertion ranging from 'a little tired' to 'getting more tired', as assessed with the OMNI Scale of perceived exertion[27]. The primary investigator will check the training intensity once again during a 15 min training session within two weeks after the start of the intervention period. This control is carried out in a home setting, so that training posture can be checked as well. When boys are not able to bicycle at a continuous speed of approximately 60 RPM without having pain or maintaining the level of 'getting more tired', the training intensity will be lowered.

As described above, training intensity is based on the ability to bicycle at a continuous speed and perceived exertion. Intensity is, thus, not based on peak heart rate, which is common in the literature on physical exercise training. The reason for this is twofold. Firstly, boys with DMD have a higher resting heart rate (110 ± 12 beats/min) compared to healthy controls (94 ± 7 beats/min )[28]. Additionally, boys with DMD are often forced to terminate a bicycle ergometry test while their peak heart rate is only 120-130 beats/min, since the main limiting factor during ergometry seems to be not their oxygen transport but their 'peripheral' capacity (muscle endurance, anaerobic power and muscle strength)[7].

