Boys are instructed to send their daily number of revolutions and their perceived levels of exertion to the primary investigator by a postal questionnaire once every two weeks, together with an overstrain questionnaire. Parents and their boys are informed by telephone when compliance is inadequate or when other problems (such as signs off overstrain: see adverse events) are identified and children are encouraged to resume the training or to adjust the training intensity.

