#### Study outcomes

Study outcomes include measurements at the levels of body functions and structures, activities and participation as defined by the International Classification of Functioning, Disability and Health (ICF) [29]. Environmental characteristics (school type and home status) are assessed at baseline. Demographic variables (age, weight and arm span), the use of medication (such as corticosteroids), any co-interventions and daily amount of physical activity are registered during each session.

The assessments of boys in the intervention group are conducted during the baseline period (T0: at baseline; T1: after 4 weeks; T2: after 8 weeks), the training period (T3: after 12 weeks; T4: after 24 weeks) and the follow-up (T5: 4 weeks after the end of the training; T6: 24 weeks after the end of the training). The assessments of boys in the control group are conducted during the baseline period (T0: at baseline; T1: after 4 weeks; T2: after 8 weeks), the control period (T3: after 12 weeks; T4: after 24 weeks), the subsequent training period (T5: after 12 weeks of training; T6: after 24 weeks of training) and during the follow-up (T7: 4 weeks after the end of the training). Assessments take place at the department of Rehabilitation of the Radboud University Nijmegen Medical Centre (T0, T2, T4, T6), but also at home (intervention group: T1, T3, T5; control group: T1, T3, T5, T7) to reduce the practical burden on the participants. All data are collected by the (trained) primary investigator (MJ). (figure 4)

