##### Primary outcomes

Bicycle ergometry: Six-Minute Bicycle Test

Muscle endurance, in this study defined as 'the ability to sustain a power without the occurrence of peripheral fatigue', is assessed with an adjusted and modified bicycle ergometer test for both the lower and upper extremities. Bicycle ergometry has been used in many studies to examine the (an)aerobic performance in healthy children and children with disabilities, and several exercise protocols are available. However, these protocols are not feasible for boys with DMD, since large muscle groups are affected in DMD and initial load and subsequent increments of load are often too hard to sustain for these patients[7,30]. Muscle endurance is, therefore, examined with a recently developed motor-assisted (passive mode 1, no-load speed 7 RPM) Six-Minute Bicycle Test by which boys are instructed to cycle as fast as possible i.e. to make as many cycling revolutions as possible. Boys start with a test for their legs and, thereafter, perform the same (arm cranking) test with their arms.

The occurrence of muscle fatigue during bicycle ergometry is assessed objectively with bipolar surface electromyography (sEMG), since peripheral fatigue is reflected as an increase in the amplitude and a decrease in the median frequency of the sEMG signal[31,32]. These parameters were found to be responsive to changes in muscle endurance during an exercise program[33,34]. Electrodes are placed unilaterally (right leg, right arm) on the m. rectus femoris, m. vastus medialis, m. biceps femoris, m. tibialis anterior, m. biceps brachii, m. triceps brachii and m. deltoideus. Electrode placement procedures will follow the recommendations for Sensor and Sensor Placement Procedures for surface electromyography[35]. Data will be registered with an EFA system (Twente Medical Systems International). The occurrence of muscle fatigue is also assessed subjectively with the OMNI Scale for perceived exertion[27]. The OMNI Scale is reliable and valid over a wide range of dynamic exercise intensities in children[27,36].

Motor Function Measure

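### Study 1 gives up blinding for a reason that covers only face-to-face testing; masked processing of stored sEMG and ultrasound data is not ruled out and not stated, and the encouraged bicycle test is collected by the investigator who monitors training

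*Protocol article*

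**What the plan says.** In the protocol article, Methods, Study 1, Design: "Assessments are not blinded, because it was considered virtually impossible to prevent the boys from revealing their group allocation to the assessor". Under Study outcomes: "All data are collected by the (trained) primary investigator".

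The first primary outcome is the Six-Minute Bicycle Test. Under Primary outcomes, "boys are instructed to cycle as fast as possible i.e. to make as many cycling revolutions as possible". The intervention section adds: "Boys are encouraged to reach as many revolutions as possible during this sub-maximal test". Fatigue during the test is measured with surface EMG (amplitude and median frequency) as the objective measure, and with a perceived-exertion scale as the subjective one. Table 2 lists quantitative muscle ultrasound (thickness and echo intensity) as a secondary outcome.

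The same investigator has a part in the training: "The primary investigator will check the training intensity once again during a 15 min training session within two weeks after the start". Also: "Boys are instructed to send their daily number of revolutions and their perceived levels of exertion to the primary investigator". This reporting is fortnightly.

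Randomisation is done by an independent statistician (Design).

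**The concern.** The article makes a stated choice and gives one reason for it. The reason is fair for live testing but is attached to assessments as a whole. An EMG file or an ultrasound image cannot tell its reader which group a boy is in unless it is labelled so. Leaving those data open would give up protection on the outcomes where masking is easiest.

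The assessor would also know the allocation whatever the boys say, because the same person checks training intensity and reads the training logs. That person collects a score that depends on how hard a boy tries and how he is urged. If encouragement differed between arms, even without intent, the revolution count would differ without any difference in endurance.

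The Discussion (Training (intensity)) expects training effects to be small, and the groups are 20 and 10, so a modest bias could matter. The multiple baseline measurements are meant for chance imbalance between groups. They do not correct a bias that arises at later visits.

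**Working it through.** The plan gives no figure to reproduce: the Sample size section says none could be calculated for the primary outcomes. The check sets the stated reason against each type of measurement in Study 1.

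- **Revolution count, live.** The boy meets the assessor, so the reason applies. The score depends on effort, encouragement is part of the procedure, and no script is described. Masking is not practical, but standardising is.
- **Motor Function Measure, live (the other primary outcome).** The reason applies, and the same investigator collects it. Coding files does nothing for it.
- **sEMG processing, after the visit.** The boy is absent, so the reason does not apply. Amplitude and median frequency are computed from a stored signal, which can be coded.
- **Ultrasound processing, after the visit.** The reason again does not apply. Stored images can be coded for arm and visit.

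The no-blinding statement therefore covers more than its reason supports. Masked processing is neither ruled out by that reason nor stated.

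**What a bias would do, if there were one.** This is an illustration only, and no bias size below is an estimate. Inputs: 20 and 10 boys (Sample size) and alpha 0.05 (Analysis), with a two-sided test assumed. It uses a simple comparison of two means rather than the planned two-way ANOVA. The true effect is zero, and b is an assumed differential bias favouring training, in SDs of the analysed score.

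- Standard error = √(1/20 + 1/10) = 0.387 SD, with 28 degrees of freedom.
- Noncentrality = b / 0.387.
- Chance of a falsely significant benefit, from the noncentral t distribution:
  - b = 0: 2.5%
  - b = 0.2 (noncentrality 0.52): 7.2%
  - b = 0.3 (0.77): 11.3%
  - b = 0.5 (1.29): 23.8%

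The article gives no SD for the bicycle test, so nothing in it shows where in this range, including zero, the trial would fall.

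**The case against.** The strongest reply is that the article discloses the lack of blinding, explains it, and calls the trial explorative. It is also a condensed account, and file handling or a test script may be set out in a full protocol or analysis plan. This largely stands against any charge of omission. It does not answer the mismatch between the printed statement and its reason. The article uses assessments for whole visits, and Table 2 has a column of that name that includes ultrasound, so a plain reading applies the statement to everything.

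Several stronger readings are tempting but not supported:

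- **That stored data are processed unmasked.** The article does not say who processes them or what that person knows.
- **That the investigator runs the training.** Boys train at home or at school. The documented role is an early intensity check and receipt of the logs.
- **That encouragement is unequal.** One instruction is given, with no difference by arm, and the person encouraging is not named. That it is the investigator is inferred from that person collecting all data. Nor does the article say that the count is visible to the boy or that scores are fed back.
- **That the trained boys' practice is a measurable blinding bias.** They are "stimulated to reach 700-1000 revolutions with both their legs and arms during each training session", so one might contrast 24 × 5 = 120 counted sessions with none in controls at T4. Table 2 as printed lists the bicycle test at T0, T2 and T5, not T4. By T5 the Study outcomes schedule gives controls 12 weeks of training, or 12 × 5 = 60 sessions. The training target over 15 minutes is also a steady 700/15 = 47 to 1000/15 = 67 revolutions per minute, whereas the test is as fast as possible. Any practice advantage is a separate matter from blinding.
- **That open file processing biases the primary comparison.** Reading sEMG or ultrasound cannot change a revolution count or a Motor Function Measure score.

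**Conclusion.** The concern holds in a limited form. The reason given for not blinding Study 1 supports open live testing only. It gives no ground for open processing of sEMG and ultrasound files, and masking of these is not stated. Separately, an effort-dependent primary outcome is collected, with encouragement, by an investigator who follows the training, and the article describes no standardisation of that encouragement.

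The size of any bias cannot be derived from the document. The percentages in the working show only that a comparison of 20 with 10 boys is sensitive to a bias of a few tenths of an SD, if one exists. They rest on an assumed bias, a two-sided test and a simple two-group comparison.

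This is an inexpensive improvement that should be made, not a flaw that invalidates the design.

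**What to change.** 1. Limit the no-blinding statement in Design to live testing.
2. Have the independent statistician replace arm and visit with a code on sEMG and ultrasound files before processing, and unmask only after the values are locked.
3. At every bicycle test, use one fixed encouragement script, identical in both arms, with no revolution count shown to the boy and no feedback on earlier scores.
4. State as limitations that the Motor Function Measure remains unmasked, that recording of the signals and images is still done live, and that the trained arm's practice on a cycling task is not removed.

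The cost is a little handling time by someone already involved in the trial and a short written procedure. Sample size, alpha and power do not change. The changes protect the processing of the fatigue and ultrasound measures and equalise encouragement at testing, and no more than that.

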#### Participants

Thirty ambulatory or recently wheelchair-dependent boys with a DNA-established diagnosis of DMD will be included (figure 2). There are an estimated four hundred boys with DMD in the Netherlands. Inclusion and exclusion criteria are described in table 1. Participants will be recruited from the Dutch Duchenne Parent Project (DPP) database. Members of the DPP will receive written information and a registration form. Additionally, we will place an advertisement on the website of the Vereniging Spierziekten Nederland (VSN), and rehabilitation physicians affiliated with the VSN will be asked to make potential participants aware of the NUD study. After registration, interested potential participants are visited by the primary investigator (MJ) at home for providing further information. Parents, and participants who are over 12 years of age, need to give written informed consent. The study protocol was approved by the Medical Ethics Committee Arnhem-Nijmegen, the Netherlands.

**Figure 2 F2:**
[figure not shown]
**Progress study 1 Dynamic leg and arm training**. This flowchart is a preliminary version. Final numbers may change depending on eligibility as recruitment is not yet complete.

**Table 1 T1:** Inclusion and exclusion criteria study 1

Inclusion criteria	Exclusion criteria
A DNA-established diagnosis of DMD	Other disabling diseases influencing mobility
Boys who are at the end of their ambulation phase, and: -need ≥5 sec. to get up from the floor or -are not able to get up from the floor or -are not able to bicycle without assistance -are dependent on a wheelchair to move over a long distance (>500 m)	Boys with a clinical symptomatic cardiomyopathy Boys <6 years old
Boys who recently became wheelchair-dependent (approximately 1-2 years after they stopped walking), and: -are able to touch the top of their head with both hands without assistance or -are not able to bicycle without assistance -are able to use a hand-operated wheelchair	

#### Intervention: dynamic leg and arm training

Boys train their legs and arms with bicycle training equipment (KPT Cycla, Kinetic, France). As this type of training equipment can be used actively or with electrical motor support, it allows a combination of active and passive bicycle training. Physical training is additional to any regular therapy or daily physical activity that boys already take part in, yet all possible co-interventions are registered.

Boys train at home or at school (depending on their preferences) during 30-min sessions (15 min leg and 15 min arm training), five days per week during 24 weeks. They are instructed to cycle with a continuous speed and stimulated to reach 700-1000 revolutions with both their legs and arms during each training session without getting too tired. Cycling characteristics are standardized (figure 3) and crank-arm length is adjusted to the child's height (e.g. a short crank-arm length for small legs and arms). Boys are free to choose when they would like to train, their training sequence (first arms or legs) and whether they want a break between the two 15 min training sessions or not. However, these training agreements are decided beforehand and registered in a training contract to which they should adhere. Additionally, the boys are recommended to train while watching television to make the training more pleasurable.

**Figure 3 F3:**
[figure not shown]
Posture during dynamic leg and arm training

Based on general training principles and based on the results from previous training studies in boys with DMD and in animal models of DMD, the training intensity is low to moderate. Intensity is determined by an adjusted and modified Six-Minute Bicycle ergometer Test (see study outcomes). Boys are encouraged to reach as many revolutions as possible during this sub-maximal test. The number of revolutions is an indication for training intensity (level of electrical assistance). After six minutes of rest, boys cycle for three more minutes at the indicated training intensity. During this period, they should be able to cycle with a continuous speed of 60 revolutions per minute (RPM) with a perceived level of exertion ranging from 'a little tired' to 'getting more tired', as assessed with the OMNI Scale of perceived exertion[27]. The primary investigator will check the training intensity once again during a 15 min training session within two weeks after the start of the intervention period. This control is carried out in a home setting, so that training posture can be checked as well. When boys are not able to bicycle at a continuous speed of approximately 60 RPM without having pain or maintaining the level of 'getting more tired', the training intensity will be lowered.

As described above, training intensity is based on the ability to bicycle at a continuous speed and perceived exertion. Intensity is, thus, not based on peak heart rate, which is common in the literature on physical exercise training. The reason for this is twofold. Firstly, boys with DMD have a higher resting heart rate (110 ± 12 beats/min) compared to healthy controls (94 ± 7 beats/min )[28]. Additionally, boys with DMD are often forced to terminate a bicycle ergometry test while their peak heart rate is only 120-130 beats/min, since the main limiting factor during ergometry seems to be not their oxygen transport but their 'peripheral' capacity (muscle endurance, anaerobic power and muscle strength)[7].

Boys are instructed to send their daily number of revolutions and their perceived levels of exertion to the primary investigator by a postal questionnaire once every two weeks, together with an overstrain questionnaire. Parents and their boys are informed by telephone when compliance is inadequate or when other problems (such as signs off overstrain: see adverse events) are identified and children are encouraged to resume the training or to adjust the training intensity.

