The currently recommended voluntary exercises to maintain comfort and symmetry[6] are widely used in daily practice and assume that low-intensity training is beneficial and not harmful for boys with DMD. However, these recommendations are mainly based on theory and there is a need for more research to justify these recommendations and to define the optimal exercise programmes[26]. As we expect that a low-intensity training may slow-down the secondary decline of muscle endurance and functional abilities (figure 1), we developed the *No Use is Disuse *(NUD) study protocol to answer the clinically relevant questions whether low-intensity physical training in boys with DMD is beneficial and does not cause further harm. The NUD study is the first to examine the effects of low-intensity physical training in human subject with DMD and will fill part of the gap in current knowledge about the possible effects of training in boys with DMD. The study consists of two training intervention studies: study 1 "Dynamic leg and arm training for ambulant and recently wheelchair-dependent boys with DMD and, study 2 "Functional training with arm support for boys with DMD who have been confined to a wheelchair already for several years". This paper describes the hypothesis and methods of the NUD study.

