#### Adverse events

All adverse events will be recorded. The study will be terminated prematurely for an individual participant when training is excessive and remains excessive after a reduction of the training intensity. Signs for overstrain are: excessive muscle pain during the training, prolonged post-exercise muscle pain, a severely uncomfortable feeling during or after the training and extreme (muscle) fatigue (OMNI scale > 6).

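### Study 1 prompts for pain, discomfort and fatigue every two weeks in the training arm only, so these symptoms cannot be compared fairly between arms

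*Protocol article*

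**What the plan says.** The Background of the protocol article sets a two-part question: "whether low-intensity physical training in boys with DMD is beneficial and does not cause further harm".

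In Study 1, 20 boys are to train and 10 are to be controls. Under Design, "the control group receives usual care (no specific intervention) during 24 weeks"; the controls train only afterwards.

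The overstrain questionnaire appears in the section on the Study 1 intervention. "Boys are instructed to send their daily number of revolutions and their perceived levels of exertion to the primary investigator" and do so "by a postal questionnaire once every two weeks, together with an overstrain questionnaire". Poor compliance or signs of overstrain lead to a telephone call and to encouragement to resume training or adjust its intensity.

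The Study 1 section on adverse events states "All adverse events will be recorded", with no restriction by arm and no account of how or when events are elicited. It then lists what counts as overstrain: "Signs for overstrain are: excessive muscle pain during the training, prolonged post-exercise muscle pain", followed by severe discomfort and extreme fatigue.

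Under Study outcomes, both arms are assessed at T3 (12 weeks) and T4 (24 weeks). Table 2 schedules fractures, falls, muscle strength, joint mobility and the Motor Function Measure at all assessments for Study 1.

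**The concern.** Muscle pain and fatigue can occur in DMD without any training. A count of such complaints in trained boys therefore needs a background rate, and a randomised control group can supply one only if its boys are asked in the same way and equally often.

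Here the form travels with a revolutions log that an untrained boy does not keep, and its result leads to advice about training that he is not doing. If symptom reports are later set side by side by arm, or if complaints that surface through the form enter the adverse event list, the training arm will show more of them partly because it was asked more. Alternatively, its symptoms may be put down to the disease, with no control rate to test that explanation. Analysis cannot repair this later, because the control data will never have been requested.

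**Working it through.** The protocol gives no figure for this point, so there is nothing to reproduce. The check is a count of scheduled prompts, followed by an illustration.

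**Inputs from the protocol article.** Randomised period 24 weeks (Design); questionnaire every two weeks (Intervention); visits T3 and T4 in both arms (Study outcomes); 20 and 10 boys (Sample size).

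**Scheduled contacts per boy in the randomised 24 weeks**

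| | Training | Control |
|---|---|---|
| Two-weekly overstrain forms | 24 / 2 = 12 | 0 |
| Visits (T3, T4) | 2 | 2 |

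**How large an artefact this could produce (assumed values).** Suppose symptom events follow a Poisson distribution with the same true mean λ per boy in both arms. Suppose also that the two-weekly forms catch every event, while visits alone catch a fraction r. Then

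- P(any recorded event, trained) = 1 − exp(−λ)
- P(any recorded event, control) = 1 − exp(−λr)

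| λ | Trained | Control, r = 0.3 | r = 0.5 | r = 0.7 |
|---|---|---|---|---|
| 0.5 | 39% | 14% | 22% | 30% |
| 1.0 | 63% | 26% | 39% | 50% |

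The true rates are equal in every row, so each gap comes from collection alone. The values of λ and r are assumptions; the protocol gives neither.

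**What equal collection could and could not show (assumed rates).** With 20 v 10 boys and a two-sided alpha of 0.05, the approximate power to detect a difference in the proportion with any symptom is:

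- 10% v 40%: 37%
- 20% v 50%: 34%
- 30% v 60%: 33%
- 10% v 60%: 80%

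Equal collection would remove the ascertainment artefact but would not make the comparison precise. That argues for description with intervals and against a test.

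**The case against.** The strongest reply is that the questionnaire is a monitoring tool and not a safety endpoint. Its signs are worded mainly around exercise, it triggers a telephone call, it is not listed in Table 2, and the Analysis section plans no between-arm comparison of it. This stands as far as it goes: an overstrain form for boys who train is proper practice and should stay. But no other structured collection of pain, discomfort and fatigue is described, and the study asks about harm.

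Second, a reader might infer that the harm question has no control-group comparison at all. The article does not support that. All adverse events are to be recorded without limit by arm. Fractures, falls, strength, joint mobility and motor function are scheduled at the same T3 and T4 assessments in both arms. These address physical deterioration and injury, a central part of the harm the article describes, and they are concurrent randomised comparisons.

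Third, the article nowhere excludes controls from the form; their omission is inferred from where the form is described and what it is sent with. Nor does it say how adverse events are elicited, and a full protocol might. The inference is nevertheless the natural one.

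Fourth, boys and assessor know the allocation, so self-reported symptoms would remain open to reporting bias even if collected equally. That is true and is a limit of the fix. It is no reason to add a second, avoidable bias. That controls train later does not help either, because it yields no concurrent untrained rate.

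**Conclusion.** The point holds for symptom-type harms. Followed as described, pain, discomfort and fatigue are prompted about 12 times per training boy and not on that schedule for controls in the randomised 24 weeks. A between-arm statement on these symptoms, or on adverse events that came to light through the form, would be biased by unequal ascertainment. Comparisons of deterioration, fractures and falls are not affected.

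The conclusion rests on reading the form as confined to boys who are training. The 12 v 0 count follows from the stated schedule on that reading; the 63% against 26-50% is only an illustration.

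A reader might also want to size the problem by the upper one-sided 95% limit when no event is seen among the 20 trained boys: 1 − 0.05^(1/20) = 13.9%. That limit depends only on the number of trained boys and would be the same after the fix, so it does not measure this defect.

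**What to change.** Leave the overstrain questionnaire as it is for monitoring the boys who train. Add a short form on muscle pain, discomfort and fatigue that does not mention training, posted every two weeks to both arms up to T4. Training boys should complete it before the overstrain questionnaire, so that the training-related items do not colour the answers.

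Report by arm the proportion of boys with any symptom and the number of reports per boy, descriptively with 95% confidence intervals. Report overstrain elicited by questionnaire separately from adverse events collected equally in both arms.

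Cost: 24 / 2 × 10 = 120 extra postal forms for controls. In the training arm the added page (12 × 20 = 240 in all) goes in a mailing that already takes place. No extra visits are needed. There is a small burden on families and some handling time. The estimates will be imprecise with 20 v 10 boys, and the self-report stays unblinded.
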